## Methods/design

### Experimental plan

The TRACES study is a multicentre, randomised, double-blinded, placebo-controlled therapeutic and pharmaco-biological dose-ranging study to evaluate the clinical efficiency of TA on blood-loss reduction in patients experiencing PPH during elective or non-emergency CS (Fig. 4).

**Fig. 4 Fig4:**
[figure not shown]
Study design

### Expert authorities and ethics committee approval

The TRACES trial obtained approval from the competent national authorities (ANSM 201500249926) and the Ethics Committee (CPP 15/50 020216) before beginning the study, in accordance with article L1121-4 of the Public Healthcare Code. This trial has been declared on the clinical trials registration under the number CT 02797119. Registration will be performed in accordance with decree dated 14 November 2006 about gathering data in the national register of individuals participating in biomedical research.

### Participating centres involved in the research programme

The five medical centres are known for their strict multidisciplinary management of PPH, including systematic measurement of blood loss, and for their ability to perform research programmes, such as the EXADELI trial. Anaesthetic and obstetric staff of each centre agreed to their participation to this study and were involved in writing the French guidelines for PPH management [22]. The study will be sponsored by The University and Regional Hospital Centre of Lille, France.

### Study population

The inclusion criteria for the experimental haemorrhagic group concern each patient experiencing a bleeding volume of more than or equal to 800 mL due to surgery or to uterine atony during an elective or non-emergency CS. This experimental group will receive a low dose or a standard dose of treatment (treatment groups) or placebo (control group). The non-haemorrhagic group, where patients experience a bleeding volume of less than 800 mL, is a reference group for biology and will be sampled to obtain a reference profile for the direct plasmin generation test in CS. All patients receive complete information, give their written consent and are covered by social security.

Non-inclusion criteria are as follows: hypersensitivity to the product or its excipient, previous or ongoing arterial or venous thrombosis, disseminated intravascular coagulopathy, except disseminated intravascular coagulopathy (DIC) associated with a predominant fibrinolytic profile, renal failure, previous seizures, severe HELLP syndrome, emergency CS, administration of TA before inclusion, inherited haemorrhagic diseases and low-molecular-weight-heparin administration within 24 h before inclusion, previous inclusion in an interventional trial for 2 months, or patient being unable to consent.

### Study protocol

#### Screening phase – information to subjects

During the routine third-trimester preanaesthestic assessment, every patient is informed about research programmes focussing on PPH and TA in haemorrhagic CS. During the preanaesthestic visit, inclusion and non-inclusion criteria are screened for; full detailed information will be given. Informed consent is signed before caesarean onset.

#### Randomisation, blinding and treatment administration – blind production of TA doses and their concentration and stability assessment

##### Description of the unit dose, packaging and labelling of the study drug

The doses will be packaged blindly for the investigators by the pharmacy of the sponsor. Each package will be numbered following the randomisation table established by centre. The package will include 10-mL syringes or flacons of the studied product. The preparation of the product in each group will be TA1 (10 mL = 1 g TA + 0 mL saline), TA½ (5 mL = 0.5 g TA + 5 mL saline) or TA0 (0 mL = 0 g TA + 10 mL saline). The master randomisation list is furnished to the pharmacy production unit to identify the packages by identification numbers containing information on the centre, on the haemorrhagic or non-haemorrhagic groups, and the inclusion number of the patient. Numbers appears clearly on packages and labels for researchers and laboratory. Unblinding envelopes are available in cases of emergency.

##### Compliance with the drug administration will be checked during the follow-up visits. All participants will be instructed to return any unused drugs to the investigator on the last follow-up visit after treatment

ᅟ

##### Methods of storing the investigational drug

The preparation of 10-mL study syringes will be achieved by the pharmacy of the sponsor in numbered boxes depending of the randomisation by centre. Every syringe and kit will be labelled according to the current regulation. The boxes are allocated to the centres via their pharmacy research unit and four boxes will be available on the labour ward in order to respond to elective or emergency inclusion processes. The product is allocated to the patient following an increasing number system. Boxes are returned to the centre pharmacy for tracing.

##### Stability study and description of the study drug production

To maintain the blind during the TRACES trial, pharmacists will be solicited to prepare ready-for-use vials containing TA (Exacyl® 0.5 g/5 mL, Sanofi-Aventis, Paris, France) at 1 g/10 mL or 0.5 g/10 mL or placebo. As the stability of TA in vials at these concentrations has not been previously studied, to our knowledge, a stability study will be performed by the toxicology laboratory of the Lille centre.

The preparation consists of adding an equal volume of 0.9% sodium chloride and TA, when diluted at 0.5 g/10 mL, and aseptically filling type I glass vials after a sterilising filtration (0.2-μm cellulose acetate filtre; Minisart®, Sartorius, France). The vials are then closed with a chlorobutyle septum.

For the stability study, 28 vials of placebo, 52 vials of TA at 0.5 g/10 mL and 52 of TA at 1 g/10 mL are prepared. Vials are stored at room temperature (below 25 °C). TA concentrations are determined using a UPLC-MS/MS method developed by the toxicology laboratory. The times of analysis are day 0, day 15, day 30, day 60, day 90, 6 months, 9 months and 1 year. For each analysis, quantification of TA is performed on three vials.

Results of the stability study are presented in Table 1.

**Table 1 Tab1:** TA concentration in vials over time

Concentration of TA (mg/mL)	Day 0	Day 15	Day 30	Day 60	Day 90	6 months	9 months	1 year
Vials with TA 0.5 g/10 mL	46 [45–47]	45,67 [44–49]	50.33 [49–52]	51 [50–52]	47.33 [46–50]	57.33 [54–61]	54.66 [53–56]	51 [50–52]
Vials with TA 1 g/10 mL	96 [93–101]	103.67 [102–109]	106 [102–112]	102.33 [102–103]	97 [96–98]	109.75 [106–114]	101.33 [101–102]	99.33 [99–100]

*TA* tranexamic acid

Moreover, the presence of potential impurities, those specified in the monograph of TA in the *European Pharmacopoeia*, was checked using gas chromatography and liquid chromatography-based methods. No impurities were found in vials up to 1 year.

During the same time, a microbiological stability test was conducted by directly seeding in a culture medium according to the *European Pharmacopoeia*. Times of seeding are day 0, day 90, 6 months and 1 year. Four tubes containing a brain-heart infusion medium with a coloured indicator will be inoculated for each concentration. Half of the media are incubated at 22 °C and the remaining at 37 °C. After being incubated for 14 days, no contamination was found.

In total, the stability of TA in glass vials for up to 1 year was demonstrated.

#### Blind randomised treatment administration

The preparation of the two dose regimens and the placebo is planned for each centre by the promoter to certify the double-blind character of the trial. The products will be prepared as ready to use

The treatment is presented in a blinded 10-mL syringe containing 0, 0.5 g or 1 g TA, respectively, for each TA0 (placebo), TA½ and TA1 group. The single-dose injection will be independent of patient weight in order to allow a pharmacokinetic analysis of the weight influence. Treatment administration is performed after birth.

The time of injection onset is noted as T0. Intravenous injection will be performed with a strict control of 1-min duration and the end of injection defines T1 = T0 + 1 min, the time of the plasma peak of TA.

Rescue administration of a second dose of 1 g TA is allowed only if haemorrhage becomes severe (more than 1500 mL). If this condition cannot be respected, the patient will be excluded a posteriori. The inclusion number will be kept for the patient presenting with this deviation and the follow-up and visits will continued and analysed in the intention-to-treat analysis.

The investigator can use, at any moment and in any situation that seems necessary, the unblinding procedure by opening the envelopes attached to the treatment.

#### Assessments

Assessments are described in Figs. 5 and 6 describing, respectively, the study protocol and the Standard Protocol Items: Recommendations for Interventional Trials (SPIRIT) flow chart and assessments at each repeated exploration time Additional file 1.

**Fig. 5 Fig5:**
[figure not shown]
Study protocol. *CS* caesarean section, *ETP-EPP* thrombin and plasmin generation potential in a well

**Fig. 6 Fig6:**
[figure not shown]
Schedule of enrolment, interventions, and assessments adapted from the Standard Protocol Items: Recommendations for Interventional Trials (SPIRIT) Figure

##### Primary endpoint: blood loss measurement method, timing and precision. The primary endpoint is the additional blood loss after injection measured at 6-h follow-up (T360)

Blood loss volume (mL) is measured in the surgical or cell-saver aspiration bag, in the delivery bag collecting vaginal blood flow during CS and by weighing drapes and pads (conversion factor for blood density = 1.06). Antiseptic and amniotic fluids must be strictly separated, counted and subtracted.

Precise blood-loss volume measurement using the physical method is guaranteed as follows: collection of the blood in a surgical or cell-saver aspiration bag is the method of measurement used in major surgery and is more precise during CS than in delivery bag collection after vaginal delivery. Drapes and pads are weighed at each observation time. Amniotic fluid, washing solutions and antiseptics are subtracted or collected in a separate aspiration bag. The investigation centres have been selected regarding their routine practice in surgical blood measurement during CS. Blood-loss calculation can be biaised by the haemodilution/haemoconcentration process and by haemolysis. However, in order to obtain a double assessment of the primary criterion, the haemoglobin-(Hb)-drop-based blood loss calculation will be performed using haemoglobin drop (last Hb measurement available before delivery as reference to day-2 final Hb) corrected by the transfused haemoglobin amount (red blood cell (RBC) concentration of 54 g/100 mL).

Secondary endpoints aim to produce scientific data for dose-ranging reduction of maternal morbidity: total blood loss, postpartum anaemia, postpartum organ failure, late postpartum side effects and death.

The pharmaco-biological substudy aims to provide data and the TA dose-ranging effect on plasmin generation and thrombin generation with regard to TA plasmatic and uterine concentration. Secondary endpoints will be measured before inclusion (T0) and at T30, T60, T120 and T360, respectively 30, 60, 120 and 360 min after inclusion and at day 2 (±12 h)

##### Safety assessments

Side effects will be recorded at each study time (Fig. 6).

High doses of TA have been implicated in the development of seizures and visual disturbances in the context of cardiac surgery. In the trauma context [27], as well as in the EXADELI trial [21], no excessive rates of complication (myocardial ischaemia, stroke, deep vein thrombosis, or renal failure) had been identified in the treated group compared to placebo. However, arterial or venous thrombotic risks must be monitored considering the prohaemostatic characteristics of the drug. Nausea and vomiting have been previously reported with TA [21].

##### Data collection

Inclusions are performed 24 h per day, 7 days a week. Each patient admitted for an elective or non-emergency CS during labour will be informed before the CS commences and a signed consent will be obtained. Patients will be included in the haemorrhagic group when haemorrhage exceeds 800 mL. Blind injection of the 10 mL-vial containing 0, 0.5 g or 1 g of TA will be performed over 1 min between T0 and T1 after injection. Transfusion, maternal haemodynamic, resuscitation measure, uterotonic and invasive procedure data and maternal morbidity parameters are recorded before inclusion (T0) and at T30, T60, T120 and T360, respectively 30, 60, 120 and 360 min after inclusion and at day 2 (±12 h) and day 42 (±14 days) postpartum. D42 data collection will be performed using telephone interview.

Various margins of time will be allowed for the timing of the data collection: T1 is the reference time and the time of the TA plasma concentration peak and no time margin will be allowed (sample exactly at the end of the TA injection). The time margins allowed for T30, T60, T120, T360 will be 5, 5, 10 and 60 min respectively. The margins allowed for day 2 will be 12 h and for day 42, 14 days. The real data collection time will be collected exactly anyway to allow the pharmacodynamic analysis.

##### Biological assessment

Preanalytical management

Tubes will be prepared in advance by the local investigator. Samples are identified by coloured codes. Samples are brought to the laboratory rapidly and current biological parameters of coagulation, blood count and renal function are performed on site and communicated directly to the clinician in charge of the patient. Concerning the TA concentration analyses and simultaneous thrombin-plasmin generation assay (STPGA), as well as any future contributive biological method to diagnose and treat fibrinolysis, plasma samples will be separated by centrifugation (2500 g × 15 min at 20 °C), then collected and frozen to be kept at − 70 °C in each centre in a box with the inclusion number and the time of sampling in order to identify the sample. At the end of the inclusions, all plasma samples will be transferred to the Biology and Pathology Centre of the Lille University Hospital in dry ice by an agreed carrier (authorised L1243-4 in the French Public Health Code).

Non-specific biological assessment

Blood for laboratory tests will be sampled using the second venous catheter currently placed as a safety procedure for CS surgery at T0 and day 2. Laboratory non-specific tests will be carried out in each centre as recommended in the French guidelines. The reference values will be collected. Laboratory non-specific tests may include complete blood count with platelet count, coagulation screening including aPTT, PT, fibrinogen, factors II and V, antithrombin, fibrin monomers and D-dimers, as well as renal function parameters. Complete blood count will be measured at the morning of day 2 after CS to obtain the comparison with the third trimester results.

Specific biological assessment

A pharmaco-biological substudy (Fig. 7) is supported by the French National Agency for Medicine and Health Products research programme and will be described in a parallel publication. Specific venous blood samples will be performed as part of the biological sampling before inclusion and at follow-up visits at T0, T30, T60, T120 and T360. Two specific tests are planned: a STPGA in a well [28], and the determination of TA concentration [29]. Both of these innovative tests will be performed on venous blood and uterine bleeding samples in order to plot a pharmacokinetic distribution of the product and its effect on fibrinolysis. The TA concentration analysis will be performed only in the haemorrhagic-patient group. A specific sample of uterine bleeding occurring intraoperatively will be performed at T0/T1 and T15 and as long as the uterine bleeding continues. A T0–T120- and T120–T360-timed urinary sample is collected in a graduated urinary bag to measure the TA urinary cumulative excretion.

**Fig. 7 Fig7:**
[figure not shown]
Ancillary pharmaco-biological substudy flow chart

#### PPH management and care standardisation

The uterotonic treatment, vascular loading and transfusion follow the French PPH guidelines, as described in the following paragraph. Uterotonic treatment respects strictly the guidelines for the prevention of PPH: systematic prophylactic infusion of oxytocin by electric syringe (10 IU in 10 min, then 10 IU over 60 min, then 10 IU over 5 h). A 5-IU intravenous bolus and a 20-IU/20-min infusion are administered in cases of uterine atony. Sulprostone or prostaglandin treatment: 500 μg in 1 h, then 500 μg over 6 h is initiated in cases of oxytocin inefficiency.

Vascular loading uses gelatin or crystalloids to compensate for exact blood loss volume exceeding 800 mL. The criteria for colloid adjustment and haemodynamic assessment are the reduction of tachycardia to less than 100 bpm, the stability of a diuresis volume at more than 40 mL/h and a systolic blood pressure over 80 mmHg. The non-invasive haemodynamic device NEXFIN® (Edwards, Philadelphia, PA, USA) should be used for this assessment. Red blood cell transfusion is strictly conducted regarding guidelines in order to maintain the haemoglobin level at more than 8 g/dL. The follow-up of the haemoglobin level use delocalised devices as repeated HemoCue® or continuous haemoglobin monitoring (Massimo®, Meaux, France). Cell salvage is used following the international guidelines. Fibrinogen concentrates can be used in association with TA when Clauss plasma fibrinogen is less than 2 g/dL and A5 FIBTEM less than 8 mm or MCF FIBTEM less than 20 mm. Prothrombinic complex concentrates, factor XIII or recombinant factor VIIa can be discussed in cases of hysterectomy. Obstetric rescue invasive procedures follow the French guidelines for PPH management in cases of persistent massive haemorrhage: intrauterine compression balloon, embolisation or surgical arterial ligatures and surgical compression techniques. Hysterectomy is considered for maternal rescue.

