#### Secondary clinical endpoints

The secondary endpoints will measure the impact of the study product and dose on total blood loss, intensity and rate of postoperative anaemia (decrease of haemoglobin preoperative to day 2, nadir of haemoglobin, number of patients with haemoglobin under 8 g/dL or a 4-point decrease at any time), immediate and late red blood cell transfusion and usage of prohaemostatic products, rate of surgical interventional procedures, such as arterial ligature, or surgical compression of the uterine wall or internal compression balloon, CS duration and general anaesthesia frequency, rate of postoperative organ failure, rate and duration of intensive care hospitalisation, breast-feeding duration, death, and the safety of the dose-ranging use of TA in haemorrhagic CS, and side effects related to the product.

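### The Clauss fibrinogen limit for fibrinogen concentrate is printed as 2 g/dL (20 g/L), which any plausible patient meets; most likely a unit slip for 2 g/L

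*Protocol article*

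**What the plan says.** The protocol article, under PPH management and care standardisation, sets out the co-treatments that apply alongside the blinded study drug. It opens by stating that uterotonics, fluid loading and transfusion "follow the French PPH guidelines, as described in the following paragraph". On fibrinogen it then says: "Fibrinogen concentrates can be used in association with TA when Clauss plasma fibrinogen is less than 2 g/dL". The sentence continues: "and A5 FIBTEM less than 8 mm or MCF FIBTEM less than 20 mm". The same section gives the red-cell transfusion target as "in order to maintain the haemoglobin level at more than 8 g/dL", where g/dL is the right unit.

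The fibrinogen sentence is permissive. Compare the rule for open tranexamic acid under Blind randomised treatment administration, which is a strict gate: "Rescue administration of a second dose of 1 g TA is allowed only if haemorrhage becomes severe (more than 1500 mL").

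Use of the product is also an outcome. The secondary clinical endpoints include "immediate and late red blood cell transfusion and usage of prohaemostatic products".

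**The concern.** An upper limit for giving fibrinogen exists to pick out patients whose fibrinogen is low. The Background section of the article describes a fall in fibrinogen as central to the coagulopathy of PPH, so this is clearly the purpose here. A limit ten times too high cannot serve it, because every patient meets it.

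At stake is the accuracy of one decision figure in the section meant to standardise care. A reader who takes the text at face value would conclude that the Clauss result plays no part in the decision and that only the FIBTEM readings restrict use. The same reader would misjudge the conditions under which prohaemostatic products were given when interpreting that secondary endpoint. The primary endpoint, its analysis and the sample size do not use this number.

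**Working it through.** **Inputs**

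- Printed Clauss limit: below 2 g/dL (PPH management and care standardisation).
- Joined conditions: A5 FIBTEM below 8 mm, MCF FIBTEM below 20 mm (same sentence).
- Plausible plasma fibrinogen: 0.5 to 10 g/L. This is an assumption from general physiology, chosen wide; the article gives no range.

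**Unit conversion**

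1 g/dL = 10 g/L, so 2 g/dL × 10 = 20 g/L.

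**Does the printed limit separate anyone?**

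| | As printed: 20 g/L | Read as 2 g/L |
|---|---|---|
| Lowest assumed value, 0.5 g/L | 0.5 / 20 = 2.5% of the limit: met | 0.5 < 2: met |
| Highest assumed value, 10 g/L | 10 / 20 = 50% of the limit: met | 10 > 2: not met |
| Result | everyone qualifies | values from 0.5 up to 2 g/L qualify, values from 2 to 10 g/L do not |

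The top of the range would have to double (20 / 10 = 2) to reach the printed limit. The conclusion does not hinge on the exact range; it would fail only if plasma fibrinogen could reach 20 g/L or more.

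**The combined rule**

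The sentence joins its three conditions with an unbracketed and/or. Write C for the Clauss condition, A for A5 and M for MCF.

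- Reading 1: C and (A or M). With C always true, this reduces to A or M.
- Reading 2: (C and A) or M. With C always true, this also reduces to A or M.

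So as printed the Clauss condition adds nothing under either reading. Once the limit is 2 g/L, the two readings differ. A patient with fibrinogen of 2 g/L or more and MCF below 20 mm fails reading 1 and passes reading 2. Correcting the unit therefore makes the bracketing matter.

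**Does the article correct itself elsewhere?**

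No. The Biological assessment section lists fibrinogen among the possible laboratory tests, without a value or unit. No other section gives a fibrinogen limit. Haemoglobin in g/dL in the same section makes a carried-over unit a plausible explanation, but the article does not state the intended unit.

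**The case against.** The strongest reply is that this is a proofreading error without consequence. Clinicians would read the figure as g/L: staff at each centre "were involved in writing the French guidelines for PPH management", and "Laboratory non-specific tests will be carried out in each centre as recommended in the French guidelines". The wording is permissive and identical for all blinded arms, so it gives no route to a biased comparison between dose groups and placebo, even for use of prohaemostatic products. The article also condenses a fuller operating protocol that may have the right unit.

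Most of this stands, and it limits the weight of the point. Literal use of 20 g/L at the bedside is not claimed, nor is any effect on an endpoint.

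Three narrower objections also deserve a reply.

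- The opening reference to the guidelines names uterotonics, fluid loading and transfusion, and the fibrinogen sentence cites no guideline of its own. Whether fibrinogen concentrate counts as transfusion is open. This is why the value should be confirmed and not simply changed.
- The laboratory section says the tests may include fibrinogen, so measurement in every patient cannot be assumed. The arithmetic does not depend on it.
- The and/or wording could be called a drafting preference. As printed it is harmless, but after the unit is corrected it changes who qualifies.

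None of these makes the printed figure right. The article states a threshold, and the threshold is wrong as written.

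**Conclusion.** The concern holds, as a minor error. The printed Clauss limit of 2 g/dL equals 20 g/L, at least twice any value in the assumed range of 0.5 to 10 g/L, so the condition does not discriminate. The conversion is certain, and non-discrimination rests only on plasma fibrinogen staying below 20 g/L. That the intended limit is 2 g/L is an inference, though a strong one: it lies inside the range and does what such a limit is for. No sample size, power or alpha figure changes. The article gives no fibrinogen values, so the number of patients affected cannot be stated.

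**What to change.** Confirm the limit against the guideline followed and print it as 2 g/L. In the same edit, bracket the condition as intended, for example: Clauss fibrinogen < 2 g/L and (A5 FIBTEM < 8 mm or MCF FIBTEM < 20 mm). Then check the full operating protocol for the same slip, and send a note to the five centres only if it is there.

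The cost is a one-line correction and one document check. It needs no new patients, procedures or data.
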